### 2.4. SLL MCP Intervention Packages

The SLL MCP interventions aim to enhance care quality for all neonates, particularly focusing on the most vulnerable small and preterm newborns, by strengthening hospitals’ ability to manage these vulnerable newborns. The SLL MCP interventions will implement a low-dose high-frequency clinical mentorship model [18] to build the competency and confidence of healthcare providers in labor and delivery, NICU, and KMC units in care provision for all neonates, with a special focus on small and preterm babies who are at risk of a range of complications.

To achieve the project’s set goal of neonatal mortality reduction, the SLL MCP interventions address three point-of-care areas: (i) labor and delivery, (ii) NICU, and (iii) KMC units. The SLL MCP package in the labor and delivery unit includes preparation for birth (confirming essential supplies such as magnesium sulphate, antibiotics, sanitizers are available, birth companion identified and prepared, delivery room is cleaned and warmed, and delivery kits prepared), essential newborn care components including resuscitation for asphyxiated newborns, CPAP at labor and delivery, prevention of infection, thermal care, early initiation and exclusive breastfeeding, and safe referral (provide pre-referral treatment, inform family on referral, prepare referral note, identify provider to accompany the newborn during referral, and arrange emergency transport service) of small and sick neonates. The SLL MCP intervention package in the NICU includes care recommendations for the level of the facility, such as management of bacterial infections including sepsis, CPAP for RDS, thermal care, and feeding management. The KMC care package consists of exclusive breastfeeding and skin-to-skin care for at least 8 h per day in line with WHO recommendations (See Figure 1).

### 2.5. Implementation Strategy

At the hospital level (Figure 2), all newborns at SLL MCP implementation hospitals will receive care immediately after birth, which includes preparing for and providing clean and safe childbirth care. During the intrapartum period, maternal and fetal statuses will be monitored, and complications will be managed, including resuscitation for asphyxiated newborns, prevention of infection, thermal care, and breastfeeding initiation. Maternal and neonatal care will continue at the postnatal care unit for 24–48 h until the mother is discharged.

Newborns will be screened for any complications. Small and/or sick newborns in need of additional and supportive care will be linked with or referred to an appropriate care facility or unit. Newborns who have complications such as RDS, sepsis, or other complications will be admitted to the NICU and receive appropriate care. Newborns who weigh less than 2000 g at birth and who are stable will be transferred to the KMC unit for continuous KMC, which includes prolonged skin-to-skin care and exclusive breastfeeding until they meet the discharge criteria (Figure 1).

Guided by the Institute for Healthcare Improvement (IHI) framework for innovation spread, the national quality strategy, and WHO maternal and newborn health quality standards, we will develop/adapt and use care at birth, NICU, and KMC quality standards, verification criteria, and assessment tools by aligning WHO recommendations with national guidelines and protocols to continuously assess the input, process, and output performance of the implementation facilities and sites. We will adapt Plan–Do–Study–Act (PDSA) continuous quality improvement cycles to use the data from quality assessments and root cause analysis using tools such as fish bone diagrams and program implementation learning to refine the implementation and improve the performance of SLL MCP implementation.

To select the hospitals that will be enrolled into the program, the regional health bureaus will use criteria including, first, for the first phase SLL MCP implementation facilities, their proximity to the previous KMC project implementation research facilities to facilitate the systematic transfer of experiences and skills gained from KMC implementation. For the second and third phase facilities, respective regions shall follow a similar approach, ensuring the proximity of the hospitals to the first phase hospitals. Second, the minimum readiness of the facilities to implement the SLL MCP interventions in terms of their healthcare providers, infrastructure, and leadership engagement. Third, the physical accessibility of the facilities to the mentoring hospital for frequent mentorship and technical support. Finally, alignment of the facilities with the government catchment/network of care facility approach to strengthen the existing government referral and linkage system.

Clinical mentors will be recruited from higher-level hospitals and receive training from trainers on the SLL MCP packages. The mentors’ competence will be evaluated using structure knowledge and skills assessment tools by senior neonatologists, obstetricians, and genealogists, who will train them, and those who acquire the necessary skills will participate in the mentorship program. Clinical mentors will similarly evaluate the knowledge and skills of physicians, midwives, and NICU nurses using structured knowledge and skills assessment tools tailored to the care the mentees provide, as well as the conditions of the space, infrastructure, and equipment in labor and delivery, NICU, and KMC units. They will then collaborate with the staff of the units and hospital leadership to develop a plan to address any gaps. The clinical mentors will reorganize the units based on these gaps to enhance the care process and provide space for neonate–mother dyads, install selected devices and equipment from hospital resources or acquired through the SLL MCP interventions, and offer ongoing, demand-driven, hands-on, catchment-based clinical mentorship and training at SLL MCP implementation facilities to improve care in labor and delivery, NICU, and KMC units. Clinical mentorship guides and tools (including mentorship process and mentees’ competency assessment tools) tailored to the care for all neonates, with a special focus on preterm and LBW newborns, will be developed in consultation with the Ministry of Health, regional health bureaus, UNICEF, the WHO, the Ethiopian Pediatric Society (EPS), the Ethiopian Society of Obstetricians and Gynecologists (ESOG), and the Ethiopia Midwives Association (EmWA). The mentorship data will be analyzed and used to inform refinement of the subsequent mentorship support. Hospitals will conduct quarterly catchment implementation learning meetings to standardize care, review performance, cross-learn experiences among facilities, and refresh their knowledge on key SLL MCP intervention areas.

### 2.6. Sample Size Estimation

While the SLL MCP interventions will be implemented in 290 hospitals consisting of primary, general, and referral hospitals, only live births and newborns treated in primary hospitals will be included and followed until their 29th day of life to estimate the impact of the intervention on neonatal mortality.

To estimate the impact of the SLL MCP interventions on neonatal mortality, the sample size required to detect a 35% reduction in neonatal mortality after implementation of the SLL MCP interventions is calculated using a sample size calculator for a stepped-wedge design. Assuming that a woreda will have a minimum population of 30,000, and with a conservative estimate of a crude birth rate of 20 births per 1000 population, there will be a minimum of 600 births per cluster (woreda) in a year. We estimated the sample size using an online sample size calculator for a stepped-wedge design (https://clusterrcts.shinyapps.io/rshinyapp/, Accessed on: 13 May 2021), considering a cross-sectional sampling structure, a discrete time decay correlation structure, 3 sequences, 0.02 ICC, and 0.8 cluster autocorrelation. The neonatal mortality under control and intervention conditions was considered to be 33 and 22 per 1000 live births, respectively, with 80% power and a 5% level of significance. The sample size required to detect a 35% reduction in neonatal mortality in the implementation sites is 12 clusters per sequence (36 clusters overall). At each phase of SLL MCP implementation, an estimated 21,600 newborns across the four implementation regions will be screened to assess neonatal outcomes.

An SLL MCP cluster will be a primary hospital that covers a woreda with an estimated minimum population of 30,000. Typically, a woreda has one primary hospital with referral linkage to a general and a referral hospital. In this evaluation design, we will progressively roll out the interventions by cluster. From the 286 woredas, the impact of the SLL MCP interventions will be measured in 36 selected woredas, hereafter referred to as evaluation clusters (9 clusters per region).

For formative assessment and program learning, qualitative data will be collected through interviews with purposively selected preterm newborns’ mothers, healthcare providers, health facility managers, mentors, and mentees involved in obstetric and newborn care, the NICU, and KMC unit at the intervention facilities. While facility assessment will be carried out in the 290 hospitals, the qualitative assessment of participants and the number required for formative assessments and program learning will be determined case by case across each phase depending on the nature of the implementation process and the hospital setting.

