### 2.3. Study Participants

The SLL MCP interventions will target all mother–neonate dyads, but will most benefit preterm and LBW newborns who are at highest risk of dying in the first month of life. To measure the impact of the SLL MCP interventions, all live births and newborns who receive care at the 36 evaluation primary hospitals are eligible for inclusion in the study. Mothers who have stillbirths will be excluded as their stillborn is not eligible to receive the SLL MCP interventions, most of which is provided starting immediately after birth.

In addition, the study will include health facility administrators, healthcare providers, mothers giving birth in hospitals and their families, and mothers and their families whose newborns are admitted to NICU and KMC units, with the goal of gathering information on the care experience of administrators and providers and on the care received by mothers and their families, especially those with premature and low birth weight newborns.

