### Limitations of the Study

The SLL MCP program is the largest facility-based neonatal care program in Ethiopia, marking a bold and ambitious step in applying implementation sciences to scale up and evaluate a large-scale health system program in the country. Nevertheless, the program’s small budget limited our capacity to plan for adequate resources to address the substantial gaps in health systems, particularly at primary hospitals. Excluding general and referral hospitals from the evaluation denominator could potentially diminish the potential impact of the program, as these hospitals are typically more prepared to implement the SLL MCP interventions than primary hospitals. Moreover, the program does not include interventions at health centers and the community level, missing out on a significant proportion of births at health centers and homes. A randomized stepped-wedge design is not feasible because the main hospitals for the three SLL MCP implementation periods will be selected by the management of the regional health offices, which does not allow for randomization. Given the resource limitations in collecting client cost data, the incremental cost analysis will be restricted to the health system perspective, without accounting for client costs. During the development of this protocol, Ethiopia was in the middle of the COVID-19 pandemic and war in Tigray. Such limitations and unforeseen challenges can pose risks in the achievement of the ambitious goal of reducing neonatal mortality by 35%.

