**Figure 2 children-13-00187-f002:**
[figure not shown]
Implementation strategy for Saving Little Lives Minimum Care package in Ethiopia. KMC: Kangaroo Mother Care, NICU: Neonatal Intensive Care Unit, CPAP: Continuous Positive Airway Pressure.

**Table 1 children-13-00187-t001:** Total expected population and birth categories in SLL MCP implementation sites in Ethiopia, 2019.

Region	Estimated Total Population	Estimated Total Annual Births	Estimated Total Annual <2500 g Births	Estimated Total Annual <2000 g Births	Estimated Total Annual Preterm Births
Tigray	5,541,997	139,455	10,599	4184	13,946
Amhara	22,192,000	342,600	76,057	10,278	34,260
Oromia	38,170,000	528,588	69,245	15,858	52,859
SNNP	10,371,000	267,233	35,008	8017	26,723
Total	76,274997	1,277,876	190,908	38,336	127,788

**Table 2 children-13-00187-t002:** A non-randomized stepped-wedge design to evaluate the coverage and impact of the SLL MCP interventions in four regions of Ethiopia, 2021.

Phases	3 Months	9 Months	3 Months	9 Months	3 Months	9 Months
Phase 1	Routine practice	Intervention *				
Phase 2	Routine practice	Routine practice	Routine practice	Intervention		
Phase 3	Routine practice	Routine practice	Routine practice	Routine practice	Routine practice	Intervention
Continuous program learning data collection, analysis, and use to inform intervention refinement and improve program performance						

* Shaded areas in the Table indicate intervention period.

**Table 3 children-13-00187-t003:** Summary of the study components, participants, and data sources.

Study Component	Design	Participants	Data Sources
Evaluation of the impact of the SLL MCP interventions	Non-randomized stepped-wedge design	Mother–newborn dyads: all live births who receive care at the 36 evaluation primary hospitals	Independent evaluation research assistants collect data by interviewing mothers and family members, reviewing medical charts and registers
Assess facility readiness, barriers, and facilitators of SLL MCP implementation	A mixed method cross-sectional formative assessment	Health facility managers, healthcare providers, and mothers who give birth at the hospitals and mothers with a (preterm) newborn/s admitted to NICU and KMC units	Facility observation, interviews with facility managers, healthcare providers, and mothers

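### The sample size takes every birth in a 30,000-person woreda (600 a year) as the cluster size, but the evaluation counts only newborns born or treated at the primary hospital, and the calculation does not match the 36-month schedule.

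*Protocol article*

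**What the plan says.** Section 2.6 (Sample Size Estimation) builds the cluster size from two planning figures: "a woreda will have a minimum population of 30,000" and "a conservative estimate of a crude birth rate of 20 births per 1000 population". Their product is the statement that "there will be a minimum of 600 births per cluster (woreda) in a year". The calculation then uses a cross-sectional stepped wedge with 3 sequences, discrete-time decay, ICC 0.02, cluster autocorrelation 0.8, neonatal mortality of 33 versus 22 per 1000, 80% power and a 5% level. It arrives at 12 clusters per sequence, 36 in all. The same section expects that in each phase "an estimated 21,600 newborns across the four implementation regions will be screened to assess neonatal outcomes".

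On who is measured, Section 2.6 says that "only live births and newborns treated in primary hospitals will be included and followed until their 29th day of life", and Section 2.3 (Study Participants) says that "all live births and newborns who receive care at the 36 evaluation primary hospitals are eligible for inclusion in the study". The Limitations section describes the program as "missing out on a significant proportion of births at health centers and homes".

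On timing, Section 2.2 gives 1 June 2021 to 30 May 2024. Table 2 divides those 36 months into alternating blocks of 3 and 9 months. Phase 1 starts the intervention after month 3, phase 2 after month 15 and phase 3 after month 27.

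**The concern.** A population multiplied by a crude birth rate counts all births in the woreda, wherever they take place. The unit observed is the hospital. Section 2.6 has no step from one to the other, and the article itself says that many births take place outside hospitals. The word minimum is therefore not earned: 600 is a floor for births in the woreda, not for newborns enrolled at the hospital.

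The schedule is a second mismatch. A three-sequence stepped wedge has four periods. Giving each period 600 births at 600 a year takes four years, and the study runs for three, with a short all-control period at the start.

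The 80% power and the 21,600 newborns per phase are presented as properties of the design. If hospitals see fewer newborns than assumed, a null mortality result could reflect lost power, and a reader relying on the stated 80% would misread it.

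**Working it through.** **Inputs from Section 2.6.** Mortality p0 = 0.033 and p1 = 0.022, so d = 0.011; ICC 0.02; cluster autocorrelation 0.8; 3 sequences; 12 clusters per sequence. The section does not say whether the 5% level is two-sided; I assume it is.

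**Cluster size and yield.** 30,000 x 20/1000 = 600 a year. 36 x 600 = 21,600, exactly the stated number per phase, so that figure also counts woreda births.

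**Model.** Generalised least squares for cluster-period means, with fixed period effects.
- Total variance s2 = [0.033 x 0.967 + 0.022 x 0.978]/2 = 0.0267.
- Covariance of periods t and s within a cluster = 0.02 x s2 x 0.8^|t-s|, plus 0.98 x s2/m_t on the diagonal, where m_t is the number of newborns in period t.
- Power (normal) = Phi(d/SE - 1.96). The t version uses clusters minus periods minus 1 degrees of freedom: 36 - 4 - 1 = 31.

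**Step 1: reproduce the plan's figure.** Four equal periods, m = 600.
- 12 per sequence: SE 0.00377, d/SE = 2.92, power 0.831 (normal), 0.806 (t).
- 11 per sequence: 0.798 (normal), 0.769 (t).

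Twelve is the smallest number that reaches 80% under either test, which matches the article.

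**Step 2: use the article's own schedule.** Four periods of 600 at 600 a year need 4 x 12 = 48 months. Table 2 collapses to periods of 3, 12, 12 and 9 months (36 in total). At 600 a year these hold 150, 600, 600 and 450 births, or 1,800 per cluster instead of 2,400. SE is 0.00395 and d/SE = 2.78, so power is 0.796 (normal) or 0.770 (t).

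**Step 3: vary hospital volume on Table 2 periods.** The documents give no hospital share or volume, so these rows are assumptions.

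| Newborns per hospital per year | As a share of 600 | Power, normal | Power, t |
|---|---|---|---|
| 900 | 150% | 0.843 | 0.820 |
| 600 | 100% | 0.796 | 0.770 |
| 480 | 80% | 0.763 | 0.735 |
| 300 | 50% | 0.676 | 0.646 |
| 150 | 25% | 0.521 | 0.490 |

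On these periods the same formula reaches 80% at about 617 newborns per hospital per year (normal; SE 0.00393) or 752 (t; SE 0.00380).

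**Step 4: the effect size.** 22/33 is a reduction of 33.3%. A 35% reduction is 33 x 0.65 = 21.45 per 1000. With 21.45 on Table 2 periods, power is 0.837 (normal) or 0.813 (t) at 600 a year, and 0.723 or 0.694 at 300 a year.

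**The case against.** The strongest reply is that 600 is a planning floor and real hospitals may well see more. Section 2.1 describes primary-level units serving 60,000 to 100,000 people. At 20 per 1000 that is 1,200 to 2,000 births, and a hospital share of 30% to 50% would give 600. Table 1 lists 1,277,876 annual births; divided by the 286 woredas of Section 2.6, that is about 4,468 each. Newborns born elsewhere but treated at the hospital are also eligible, which adds to volume, although the Discussion frames the hypothesis around inborn neonates. This objection stands as to direction: the documents do not show that volume is below 600. It does not rescue the calculation, because Section 2.6 makes no such argument.

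Three stronger readings should be set aside.
- A reader might infer that the trial is underpowered. That needs hospital volumes, which are not given. The sentence in the Limitations section concerns program coverage and carries no number.
- A reader might infer from Table 1 that 20 births per 1000 is too high, since the pooled rate is 16.8, with Amhara 15.4 and Oromia 13.8. But Tigray is 25.2 and SNNP 25.8. With nine clusters per region the unweighted mean applies: (25.2 + 15.4 + 13.8 + 25.8)/4 = 20.05. Table 1 does not contradict 20 for this sample.
- A reader might infer that 12 per sequence can arise only from four equal periods of 600. It cannot be pinned down that way: a 35% effect on Table 2 periods also exceeds 80% (Step 4), and the calculator's period-size entry is not shown.

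Finally, the schedule shortfall alone is small: 0.796 against 0.80 by the normal test, less than the gap between the two tests.

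**Conclusion.** The concern holds as a wrong-unit input and a schedule mismatch behind a stated power and sample size. Cluster size and newborns per phase count woreda births, while the study enrols hospital newborns. On the printed 33 versus 22 per 1000 and the Table 2 schedule, 36 clusters give 0.80 (normal) or 0.77 (t) if each hospital sees 600 a year. For 80%, 50% and 25% of that volume the figures are 0.74 to 0.76, 0.65 to 0.68 and 0.49 to 0.52; at 900 a year they are 0.82 to 0.84. The shares are assumed, and the results rest on a two-sided test, equal volume across hospitals, the stated correlations and Table 2 collapsed to four periods. Neither the size nor the sign of the error can be settled from the documents. What can be said is that the 80% power is not supported by the inputs as written.

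**What to change.** In Section 2.6, replace 600 with the expected annual number of eligible newborns at the 36 primary hospitals, saying whether outborn newborns are counted. Sections 2.7.1 and 2.7.2 already name the sources: labor and delivery and NICU logbooks, and DHIS2. Section 2.7.2 admits quality gaps in DHIS2, so check its counts against the registers.

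Rerun the calculation on the Table 2 periods (3, 12, 12 and 9 months) with one consistent effect, either 22 per 1000 described as a 33.3% reduction or 21.45 described as 35%. State the test used, then report the achieved power or the detectable reduction and correct the expected newborns per phase. Keep the 36 hospitals.

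The cost is collecting the counts, about an hour of recalculation, and revised text. The stated power may come out less favourable.

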## Abstract

Background: Neonatal mortality remains a significant public health challenge in Ethiopia. Despite efforts to implement key evidence-based interventions, their coverage and utilization remain low. The Saving Little Lives (SLL) program aims to scale-up a Minimum Care Package (MCP) of synergistic, life-saving interventions for all liveborn neonates, with a focus on preterm and low birth weight (LBW) infants, across 290 hospitals in Ethiopia (206 primary, 69 general, and 15 referral hospitals), representing 82% of all hospitals in the country at the time of the study, and evaluate the impact on neonatal mortality. Methods: A non-randomized stepped-wedge trial will be conducted to evaluate the impact of implementing the SLL MCP interventions. Quantitative evaluation data will be collected from 36 primary hospitals, selected from 206 primary hospitals across four regions, receiving the interventions. An independent evaluation research assistant will be deployed in each of the hospitals to collect data using Open Data Kit (ODK) through interviewing mothers before discharge, on the 29th day of life if discharged, and reviewing medical records. A mixed-method, cross-sectional formative assessment will be conducted prior to implementation, employing quantitative facility assessment and qualitative interviews with mothers, healthcare providers, and facility managers. This will be followed by continuous program learning assessment once implementation begins. Descriptive data will be presented using numbers, percentages, tables, and graphs. Regression modeling and generalized estimating equations (GEEs) will be used to estimate the impact of the SLL MCP interventions. Qualitative data will be gathered through in-depth interviews, digitally recorded, transcribed, and thematically analyzed using ATLAS.ti Version 7.5 software to assess facility readiness, barriers, and enablers of implementing the SLL MCP interventions. Expected Outcome: We hypothesize that achieving 80% coverage of the SLL MCP interventions among eligible neonates will result in a 35% reduction in neonatal mortality at implementation facilities.

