The Ethiopian Newborn and Child Survival and Development Strategy prioritizes antenatal corticosteroids for preterm labor, neonatal resuscitation and respiratory support, KMC, antibiotics for neonatal sepsis, and early initiation and exclusive breastfeeding as key interventions to improve neonatal survival [7]. Furthermore, Ethiopia has been making substantial national investments to improve neonatal care across the health system, as articulated in strategic documents, strategies, and guidelines [12,13]. These strategy documents provide guidance for achieving a substantial reduction in neonatal mortality (to 21 deaths per 1000 live births) by 2025 [14]. However, Ethiopia remains among the five countries with the highest neonatal mortality rates [1]. More importantly, the coverage of key interventions remains low, resulting in high neonatal mortality rates.

Building on the lessons learned from the successful scale-up of KMC implementation research conducted in collaboration with the WHO to scale up KMC in four major regions of the country between 2016 and 2019 [15], the SLL MCP program aims to scale up lifesaving interventions for eligible liveborn infants, with a focus on preterm and LBW newborns. We hypothesized that the estimated mortality reduction target will be met by achieving 80% coverage of an evidence-based bundle of interventions for eligible neonates during childbirth, in the NICU, and in the KMC unit, with a focus on preterm and LBW newborns, in 290 hospitals across four regions in Ethiopia over a three-year implementation period. Given that the hospitals covered by the SLL MCP program represent 82% of the total 353 hospitals operating in the country [16], and in accordance with the government’s strategy for comprehensive newborn care and leveraging the existing structures of the national and regional health system, led by the government, the objective of this project is to reduce neonatal mortality by 35% in the implementation centers, measuring the coverage and impact of implementing the SLL MCP interventions on neonatal mortality.

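### The 36 clusters are said to be sized for a 35% reduction in neonatal mortality, but the rates entered (33 and 22 per 1000) are a 33.3% reduction; the slip is conservative

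*Protocol article*

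**What the plan says.** Section 2.6 of the protocol article opens the calculation by naming its target, "the sample size required to detect a 35% reduction in neonatal mortality after implementation of the SLL MCP interventions", and closes it with the same figure: "The sample size required to detect a 35% reduction in neonatal mortality in the implementation sites is 12 clusters per sequence", 36 overall.

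Between these two sentences stand the inputs. The rates are given as "The neonatal mortality under control and intervention conditions was considered to be 33 and 22 per 1000 live births, respectively". Power is set at 80% and the significance level at 5%. The design inputs are listed as "considering a cross-sectional sampling structure, a discrete time decay correlation structure, 3 sequences, 0.02 ICC, and 0.8 cluster autocorrelation". On cluster size the section says that "there will be a minimum of 600 births per cluster (woreda) in a year".

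The 35% also appears outside the sample-size section. The Abstract hypothesises that 80% coverage "will result in a 35% reduction in neonatal mortality at implementation facilities", and the Introduction says that "the objective of this project is to reduce neonatal mortality by 35% in the implementation centers". The Discussion repeats it as the hypothesis, and the limitations section calls it an ambitious goal.

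**The concern.** One calculation is described by two effect sizes that cannot both be right. The text before and after the inputs says 35%; the two mortality rates imply one third. Section 2.6 does not call 22 a rounded or approximate value, and rounding 21.45 to the nearest whole number would give 21, not 22.

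At stake is whether the published requirement can be traced. Someone who enters an exact 35% reduction in the cited calculator should not expect to get 12 per sequence back, and someone who quotes the article will attach the 80% power to the wrong effect. The direction also has to be settled: had the entered effect been larger than the named one, the trial would be short of clusters for its own target.

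**Working it through.** **Step 1. The effect actually entered.**
- Reduction implied by the rates in Section 2.6: 1 − 22/33 = 0.333, or 33.3%.
- Rate implied by the named 35%: 33 × (1 − 0.35) = 21.45 per 1000.
- Gap: 22 − 21.45 = 0.55 deaths per 1000. For comparison, 21 per 1000 would be 1 − 21/33 = 36.4%.

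**Step 2. Inputs for the power check.**
- From Section 2.6: 3 sequences, cross-sectional sampling, discrete-time decay, ICC 0.02, cluster autocorrelation 0.8, 5% significance, 80% power, control rate 33 per 1000.
- Assumed, because the article does not say: a two-sided test; four periods (one with all clusters in control, then one crossover step per sequence); and 600 births per cluster-period. The article gives 600 per cluster per year. Its figure of 21,600 newborns per phase equals 36 × 600, which supports 600 per period.

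**Step 3. Formula.** Generalised least squares on cluster-period means, with a fixed effect for each period:
- total variance s² = [p₁(1 − p₁) + p₂(1 − p₂)]/2;
- covariance of two period means in one cluster = s² × 0.02 × 0.8^|t − u|, plus s² × 0.98/600 when t = u;
- power = Φ(|p₁ − p₂|/SE − 1.96), where SE is the standard error of the intervention effect and is proportional to 1/√(clusters per sequence).

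**Step 4. Reproduce the plan's figure (33 versus 22).** s² = 0.026714.
- 11 per sequence: SE = 0.00394; 0.011/SE = 2.793; power 79.8%.
- 12 per sequence: SE = 0.00377; 0.011/SE = 2.917; power 83.1%.

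The smallest number that reaches 80% is 12, which matches the article.

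**Step 5. Repeat for a true 35% reduction (33 versus 21.45).** s² = 0.026450.
- 9 per sequence: SE = 0.00433; 0.01155/SE = 2.666; power 76.0%.
- 10 per sequence: SE = 0.00411; 0.01155/SE = 2.810; power 80.2%.
- 12 per sequence: SE = 0.00375; 0.01155/SE = 3.078; power 86.8%.

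The requirement falls to 10 per sequence, or 30 clusters, and the planned 12 have about 87% power.

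**Step 6. Does the direction depend on the assumed layout?** Clusters per sequence needed for 80% power:

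| Layout | 22 per 1000 | 21.45 per 1000 |
|---|---|---|
| 4 periods of 600 | 12 | 10 |
| 4 periods of 450 | 13 | 11 |
| 4 periods of 300 | 15 | 13 |
| 3 periods of 600 | 15 | 13 |

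The absolute numbers move with the layout. The direction does not: in each row the named 35% needs fewer clusters than the entered 33.3%.

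**The case against.** The strongest reply is that nothing of substance is harmed. The trial was sized for a slightly smaller effect than it hopes for, which is ordinary prudence, and a design with 80% power for 33.3% has more than 80% for 35%. On the inputs above, the assurance of at least 80% power for a 35% reduction with 36 clusters is true. This stands, and it makes the point a minor one. It does not remove the mismatch, because the article calls 12 per sequence the number required for 35%, and on the inputs that reproduce 12 that number is 10.

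Two stronger readings are tempting.

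- A reader might infer that a trial which observed exactly its planned rate of 22 per 1000 would miss its own 35% target and so fail. The article does not support this. It treats 35% as a hypothesis, a programme objective and a goal, and nowhere makes an observed 35% reduction a criterion of success. The analysis section plans regression with GEE and sets no such margin. A trial powered at exactly 35% could also observe less.
- A reader might take the alternating 3- and 9-month periods of Table 2 and conclude that the choice between 22 and 21.45 decides whether power reaches 80%. That cannot be established. The births per period and the way the correlation decays over unequal periods are not stated, and power for 22 on that layout runs from about 77% to 89% as the correlation assumption changes. Any shortfall there would come from the period layout rather than from this mismatch.

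**Conclusion.** Section 2.6 is wrong as written: the effect it names (35%) is not the effect it entered (33.3%, a difference of 0.55 deaths per 1000 in the intervention rate). That part is plain arithmetic and rests on no assumption.

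The consequence is small and favourable. With four periods of 600 births per cluster and a two-sided 5% test, both assumed, the stated 12 per sequence is reproduced for 33 versus 22, while an exact 35% reduction needs two fewer per sequence and gains 86.8 − 83.1 = 3.7 percentage points of power with the planned number. The mismatch gives no reason to add hospitals, alter the analysis or lower the programme goal. A goal and a planning effect may differ, provided each is labelled correctly.

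**What to change.** Preferred: in Section 2.6, keep 33 and 22 per 1000, replace the two mentions of 35% with a statement that the 36 clusters are sized for a one-third (33.3%) reduction, and add that power for the 35% programme goal is higher.

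Alternative: re-run the calculator with 21.45 per 1000 and report both the number of clusters then required and the power of the planned 36. Changing the rate alone would not be enough, because the sentence giving 12 per sequence as the requirement would then need rewording too.

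Either way it helps to state the number of periods and the births per cluster-period that were entered, so that the figure can be reproduced. The cost is a few sentences, plus one calculator run for the alternative. The 36 hospitals stay, and the 35% in the Abstract, Introduction and Discussion can stand as the programme's goal.
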